## METHODS

5

### Interventions

5.1

#### Intervention arm: T‐Control catheter

5.1.1

The T‐control catheter is a flexible, silicone tube with an inflatable balloon at the distal tip, a polytetrafluoroethylene (PTFE) membrane integrated into its body, and a sliding fluid control valve. The valve, built into the catheter, provides additional functions to the catheter, such as turning urine flow on and off after insertion (functions currently provided by accessories such as caps or valves) and controlling urination during the insertion process (function not provided by any other device). Accidental loss of urine can thus be avoided from the first moment of use until its withdrawal. In addition, it has a safety cap that reduces the possibility of accidental valve movements before use or during transport and fixing. The design has been developed in such a way that, once inserted, it facilitates autonomous use even for the elderly or patients with limited manual dexterity. The device is sterile and single‐use, like any conventional Foley catheter.

The continuous use of a single device of T‐Control cannot exceed 30 days. The cumulative use for each type of T‐Control device can exceed 30 days.

T‐Control is manufactured, sterilized, and packaged by the subcontracted company Conod Medical Co., Ltd under the specifications of Rethink Medical and under its quality standards, as well as its accessory holder, also manufactured and packaged by the same subcontracted company.

#### Control arm: Foley catheter

5.1.2

Silicone Foley catheters are transurethral balloon catheters used to treat bladder emptying disorders, as well as drain urine from the urinary tract, continuous fluid irrigation, and/or medication administration. It is suitable to be used for a prolonged period of no more than 29 days and in Urology, Internal Medicine, Surgery, Obstetrics, and Gynaecology Services.

For this arm, conventional two‐way silicone Foley‐type catheters will be used. They consist of a body, drainage funnel, inflation funnel, and balloon valve. The product is sterile and single use.

### Study procedures

5.2

The flowchart in Figure 1 describes the participant timeline throughout the study. The catheter will be inserted by the research staff after obtaining informed consent (Data S8), and the inclusion and randomization of the participants. The healthcare professional who inserts the catheter must have experience in bladder catheterization. Professionals without sufficient experience in catheterization involved in the study will receive specific training prior to the start of the study. In addition, the research staff will receive specific training on the device prior to the start of the study (Data S1). All the staff involved in the study will have access to the user instructions at any time.

**FIGURE 1 bco2313-fig-0001:**
[figure not shown]
Flow diagram describing the participant timeline through the clinical trial. EQ‐5D‐5L, EuroQol questionnaire—five dimensions—five levels; QoL, quality of life; UTI, urinary tract infections.

After catheter insertion, participants and their family, friends, or other informal caregivers will receive information about wearing an indwelling urinary catheter and specific information about the device randomly inserted, the standard Foley or the T‐Control catheter (Data S2). Standard catheter care is permitted during the trial both managed by the participants or participants' caregivers. In addition, patients will receive an incident diary (Data S4) in which they can record any incident during the bladder catheterization period. Four weeks after indwelling bladder catheter insertion, patients will be contacted by the urology outpatients department for a follow‐up visit, during which the study catheter will be removed and Clinical Data Notebook completed (Data S3).

Finally, after the follow‐up visit, a patient subgroup will take part in the discussion groups to evaluate their acceptability of the device used as well as their experiences, preferences, and needs (at which point their contribution to the research will finish).

Health professionals who have participated in the study will complete at closure, and after signing the informed consent form, a survey where they will evaluate their level of satisfaction and workload perceived for both types of catheters included in the study (Data S7).

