#### Criteria for discontinuing or modifying allocated interventions

5.2.1

Reasons for going off or discontinuing the trial are as follows:
Adverse events that may compromise the patient's safety;Need for antibiotic treatment for a reason unrelated to the use of a bladder catheter;The patient's refusal to continue (in the event that, according to clinical practice, they still needed to carry an indwelling bladder catheter, the T‐Control catheter would be exchanged for the conventional Foley‐type catheter); andDeath.

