### Methods of data collection

5.4

The source and timing of measures are summarized in Table 1. In accordance with the proposed research objectives, the outcome measures that will be performed are the following.

**TABLE 1 bco2313-tbl-0001:** Source and timing of variables obtained for the study.

Variable	Method of obtention	Data collection format	Source	Timing			
				Baseline	4 weeks	Up 6 months AFUV	Close‐out
Baseline data (sociodemographic, clinical, and life habits)	Personal interview/PCDN	Paper/electronic	P and HP	X			
Magnitude of infection	Urine culture/PCDN	Paper/electronic	Microbiology laboratory	X	X		
Rate of infection (asymptomatic and symptomatic UTI)	Urine culture/PCDN	Paper/electronic	Microbiology laboratory	X	X		
Adverse events during catheter insertion	Observation/PCDN	Paper/electronic	HP	X			
Adverse events during catheterization time	ID/PCDN	Paper/electronic	P		X		
Catheter biofilm	Viable cells counting/PCDN	Paper/electronic	Microbiology laboratory		X		
Antibiotic treatments related to catheterization	ID/PCDN	Paper/electronic	P and HP		X		
Healthcare resources utilization	ID/PCDN	Paper/electronic	P and HP		X		
Quantitative data for QoL and catheter satisfaction	Patients' questionnaire and EuroQoL 5D questionnaire	Paper/electronic	P	X	X		
Qualitative findings for acceptability and experience	Discussion groups	Audio recording	P			X	
Catheter opinion (professionals)	Professional questionnaire	Paper/electronic	HP				X
Workload perceived	NASA‐TLX questionnaire	Paper/electronic	HP				X

Abbreviations: AFUV, after follow‐up visit; EuroQoL 5D, EuroQol questionnaire—five dimensions—five levels; HP, health professional; ID, incident diary; NASA‐TLX, NASA Task Load Index questionnaire; P, participant/relative, friend, or informal carer‐completed questionnaire; PCDN, Patient Clinical Data Notebook; QoL, quality of life perceived; UTI, urinary tract infections.

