##### Rate of symptomatic and asymptomatic infections

The magnitude of infection obtained from the urine samples will be classified according to the following criteria based on the European Association of Urology (EAU) clinical guidelines^29^:
Symptomatic infection: The presence of pathogenic microorganisms in amounts greater or equal to 1000 Colony Forming Units/mL (CFU/mL) accompanied with symptoms will determine the existence of the infection.Asymptomatic infection: In the absence of infection symptoms, a quantity of microorganisms greater than or equal to 100 000 CFU/mL will indicate asymptomatic infection.

In addition to the presence or absence of infections to assess their rate, this variable will also be collected using the outcome measure “infection‐free days” (with a maximum possible value of 28 days) to be compared between Foley‐type catheters and T‐Control. Suppose the patient at some point prior to the follow‐up visit presents symptoms compatible with UTI. In that case, a urine culture will be performed to confirm the presence or absence of urinary infection, according to usual clinical practice. In the event that the patient receives an antibiotic for a UTI while he/she takes part in the study prior to the follow‐up visit, this will be recorded in the medical record. However, the patient will also be asked about it at the follow‐up visit when he hands in his/her incident diary, and this will be counted as an infection.

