##### Number of adverse events related to catheterization

The type and number of adverse events will be registered in the Patient's Clinical Data Notebook: accidental disconnection of the catheter, obstruction, pain, loss of urine per catheter, haematuria, and accidental spills caused by the professional during insertion. The patient will receive a Patient Incident Diary to write down the incidents, along with other information that may be of interest during catheterization. Timing and source of adverse events data are summarized in Table 1.

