##### Healthcare resource use

The costs arising from catheterization, such as the consumption of consumable materials and resources and diagnostic tests (urine cultures and catheter cultures and biofilm analysis), will be collected in the Patient's Clinical Data Notebook and will be evaluated from the public healthcare services perspective. The analysis will also include costs because of patient contacts with primary care services, hospital admissions and length of stay, outpatient visits, emergency attendance, and medications prescribed during the study period. The information related to healthcare resource use will be drawn from each patient's electronic clinical record.

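### Table 1 makes unblinded patient or carer report the only named source of adverse events during catheterization, although the clinical record is already being extracted for costs

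*Protocol article*

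**What the plan says.** Section 3 of the protocol article makes the number and relevance of catheter-related adverse events a secondary endpoint compared between arms. Four places describe how those events are collected.

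- **Section 5.2, Study procedures.** Patients receive an incident diary "in which they can record any incident during the bladder catheterization period". The 4-week follow-up visit is the one "during which the study catheter will be removed and Clinical Data Notebook completed".
- **Section 5.4, Table 1.** The row "Adverse events during catheterization time" has the incident diary and Clinical Data Notebook as method, P as source, and 4 weeks as timing. The footnote defines the code as "P, participant/relative, friend, or informal carer".
- **Section 5.4.2, number of adverse events.** "The type and number of adverse events will be registered in the Patient's Clinical Data Notebook". A list of event types follows, and the reader is sent to Table 1 for timing and source.
- **Section 5.4.2, rate of infections.** The diary comes back at the follow-up visit; the patient is asked there about antibiotics "when he hands in his/her incident diary".

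For costs, Section 5.4.2 on healthcare resource use covers primary-care contacts and "hospital admissions and length of stay, outpatient visits, emergency attendance, and medications prescribed during the study period", taken from each patient's electronic clinical record. Section 2.4 states that participants, health professionals, the research team and monitors are not blinded; the data analysis and the laboratories are.

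**The concern.** A comparative safety endpoint has, for the whole dwell period, one named source: people who know which catheter was fitted, using a diary whose wording permits entries without requiring them. If patients in one arm note or recall incidents more readily than in the other, the event counts differ without any difference between the devices.

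The article also describes a second source that does not depend on the patient's memory or opinion of the device, and uses it for costs only. A patient seen in the emergency department for an obstructed catheter, who neither writes it down nor mentions it at the visit, could appear in the resource-use data and be absent from the obstruction count. The trial's safety and economic results could then disagree, with no stated rule for resolving this. With 25 patients per arm, a few unrecorded events are enough to change how the comparison reads.

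**Working it through.** There is no stated figure to reproduce; this is a question of what the document fixes as a source.

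**Step 1. Compare the relevant rows of Table 1.**

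| Row | Method | Source | Timing |
|---|---|---|---|
| Adverse events at insertion | Observation and notebook | HP | Baseline |
| Adverse events during catheterization | Diary and notebook | P | 4 weeks |
| Antibiotic treatments | Diary and notebook | P and HP | 4 weeks |
| Healthcare resource use | Diary and notebook | P and HP | 4 weeks |

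The last three rows share method and timing. Only the adverse-event row omits the health professional.

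**Step 2. Look for another source in the text.** The adverse-event paragraph of Section 5.4.2 defers to Table 1 for source, so the P entry is the operative rule. For resource use, Table 1 does not mention the clinical record but the text of Section 5.4.2 does. For antibiotics given for a urinary infection, Section 5.4.2 uses the medical record and also asks the patient. For adverse events during catheterization, neither table nor text names the record.

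**Step 3. See whether Section 5.6 fills the gap.** Regular staff contact with subjects is given there as a means of retention and of ensuring that outcome measures are collected. The external monitor's contacts are with the centres. Table 1 lists no adverse-event collection between baseline and 4 weeks.

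**Step 4. Ask which events are exposed.** Section 5.4.2 lists accidental disconnection, obstruction, pain, urine loss, haematuria, and spills caused by the professional at insertion. The last belongs to insertion and is observed by staff. The other five can arise during the dwell period, when their recording depends largely on the patient noticing and reporting them.

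**Step 5. Illustrate the sensitivity. All inputs here are assumptions except n = 25 per arm (Section 5.3).** Let the true risk p be equal in both arms and let c be the proportion of affected patients whose event is reported.

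- Expected reported cases = 25 × p × c. Apparent risk ratio = c₂ / c₁, whatever the value of p.
- Take p = 0.40 and c₁ = 0.90: 25 × 0.40 × 0.90 = 9.0 reported cases in the first arm.
- c₂ = 0.90: 9.0 cases, ratio 0.90 / 0.90 = 1.00.
- c₂ = 0.70: 25 × 0.40 × 0.70 = 7.0 cases, ratio 0.70 / 0.90 = 0.78.
- c₂ = 0.50: 25 × 0.40 × 0.50 = 5.0 cases, ratio 0.50 / 0.90 = 0.56.

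Exchanging the arms reverses the direction: 0.90 / 0.70 = 1.29. The article gives no reporting rates, so these figures show only how the comparison responds to unequal capture. They do not estimate a bias.

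**The case against.** The strongest reply is that the diary is not the only instrument. Events are registered in the Clinical Data Notebook, against a named list, at a visit where the patient is present and can be asked. That stands: it would be wrong to say that adverse events come only from an optional diary. But the notebook is where events are written down, and Table 1 still names the patient or carer as the sole source of what goes into it.

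A second reply is that some resource-use data go into the same notebook, and nothing forbids staff from transferring an obstruction found in the record to the adverse-event section. The notebook and diary templates (Data S3 and S4) are not shown and may say so. This limits the finding to the source rule as written; it does not remove the mismatch within Table 1.

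A third reply is that lack of blinding is already acknowledged in Section 6, and that a new device could prompt more reporting as easily as less. Both are correct. No direction can be claimed.

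A reader might go further and infer that serious events will be missed, or go unacted on for up to four weeks because the diary is returned only then. The article does not support this. The discontinuation criterion "Adverse events that may compromise the patient's safety" in Section 5.2.1 is not tied to the diary. Section 2.4 provides for unmasking when safety is at stake. Section 5.4.2 describes urine culture and recording of antibiotics before the follow-up visit. Section 5.6 has monitoring that covers safety issues and onward reporting. Procedures for serious events may also be in the full protocol, which is not shown.

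**Conclusion.** The point holds as a defect in a stated source rule. As written, a between-arm secondary endpoint rests on unblinded patient or carer report during catheterization, while the neighbouring rows add the health professional and the clinical record is extracted for costs but not named for this purpose. The comparison is therefore open to incomplete and possibly differential reporting, and to disagreement with the resource-use data.

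The size and direction are unknown. Differential reporting is a plausible risk of open-label self-report, not something the article demonstrates. The conclusion assumes that Table 1 is followed literally and that the unshown notebook does not already require a check against the record. It concerns one secondary endpoint of a 50-patient pilot and does not touch the primary endpoints or the sample size.

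**What to change.** 1. In Table 1, change the source for adverse events during catheterization from P to P and HP plus the electronic clinical record.
2. At the 4-week visit, ask the event list of Section 5.4.2 as the same structured questions in both arms, whatever the diary contains, and enter the answers in the notebook.
3. Reconcile those answers with the emergency, admission, outpatient and primary-care contacts already extracted for costs. Add an event only where the record documents a listed adverse event, for example obstruction, haematuria or accidental disconnection. Routine or planned catheter contacts, including the 4-week visit itself, are not events.

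The cost is one table entry, a short set of questions at an existing visit, and a brief reconciliation per patient from records already in use. Reported event counts are likely to rise somewhat. The change will not correct differential reporting of minor events, such as pain or leakage, that lead to no healthcare contact. For those the patient remains the natural source, and the report should say that they are open-label self-reports.

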#### Criteria for discontinuing or modifying allocated interventions

5.2.1

Reasons for going off or discontinuing the trial are as follows:
Adverse events that may compromise the patient's safety;Need for antibiotic treatment for a reason unrelated to the use of a bladder catheter;The patient's refusal to continue (in the event that, according to clinical practice, they still needed to carry an indwelling bladder catheter, the T‐Control catheter would be exchanged for the conventional Foley‐type catheter); andDeath.

### Sample size determination

5.3

The sample size for the quantitative primary endpoint “degree of satisfaction and levels of self‐perceived health‐related quality of life of patients” has been calculated in terms of standardized differences through Cohen's delta. Assuming a significance level of 2.5%, given that the endpoint is composed of two different questionnaires (EuroQol‐5D‐5L [EQ‐5D‐5L] and Catheter‐related quality of life questionnaires), and expecting large differences (0.95) between groups, a sample size of 25 per group would be enough, taking into account a dropout rate of 5%.

Regarding the qualitative primary endpoint, it is expected to reach information saturation with a maximum of four discussion groups composed of between 8 and 10 participants (a total of a maximum of 40 subjects), so the calculated sample size is considered sufficient.

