### Random assignment

2.3

Participants will be assigned 1:1 to one of the two trial arms of the quantitative study by a local research team member using a centralized computerized randomization system (RAND2 software, The MathWorks Inc, Natick, USA, administered by the data management team, depending on the contract research organization [CRO]).

The blinded allocation sequence is concealed by the use of a centralized computerized randomization system. The personnel responsible for catheter insertion will enrol subjects on the randomization system.

The patient's identifying number will be consecutively assigned, and inclusion in the intervention group or control group will be carried out through the randomized numerical distribution generated by a random online generator.

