##### Self‐perceived health‐related quality of life

The following instruments are administered to patients:
EQ‐5D‐5L^27^: This is a generic health‐related quality of life questionnaire that evaluates five domains: mobility, self‐care, usual activity, pain/discomfort, and anxiety/depression. Each domain is scored on a 5‐point scale, which yields a descriptive system that can be combined into a five‐digit number reporting the patient's state of health. Each EQ‐5D‐5L health state can be converted to a single summary index by applying a formula that attaches weights to each level in each dimension. A number of formulae or value sets are available for different countries, based on the valuation of EQ‐5D health states from general population samples. In this study, the value set estimated for Spain by Ramos‐Goñi et al.^28^ will be used. After applying these weights, the range of the summary index is 1 (perfect health) to 0 (health state equivalent to death). Negative values represent health states considered to be worse than death. The questionnaire also includes a visual analogue scale where responders are asked to indicate their health status on the day of the interview, ranging from 0 (worst possible health) to 100 (best possible health).Catheter‐related quality of life questionnaire: To evaluate the specific health‐related quality of life for long‐term catheterized patients, Rethink Medical has developed two specific instruments created in the context of this project based on the experience of our previous studies (Patient's workshop).^25^ The first one (Data S5), administered during the initial visit, consists of 47 questions, related to the patient's experience and journey with catheterization before the study, as baseline data. The questions are related to the type of catheter and accessories used, the experience of catheterization, emotions felt at the beginning (right from the moment of the prescription), satisfaction and comfort with the catheter, complications associated with catheter use, usability and complications associated with accessories and changes in the personal habits caused by the catheter's use, and how these issues have affected their lives. The second one (Data S6), administered during the follow‐up visit, consists of the same questions as the first one (but referred to the catheter and accessories used during the study) plus four questions related to information received when catheterized for the first time (total 51 questions). In order to quantitatively evaluate the answers, statements will include single answers with scores on a scale from 0 to 10, 0 to 5, and 0 to 4 for both questionnaires. The questionnaire devised by Rethink Medical is expected to be validated during the clinical study in conjunction with another study specially designed for its validation.

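### The 2.5% level in 5.3 holds the primary family error at 5% only with one prespecified score per questionnaire; 5.4.1 names no such pair, and 5.7 prints a different threshold

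*Protocol article*

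**What the plan says.** Section 5.3 (Sample size determination) treats satisfaction and health-related quality of life as one quantitative primary endpoint measured by two questionnaires, and sets the level accordingly: "Assuming a significance level of 2.5%, given that the endpoint is composed of two different questionnaires". The sample size "has been calculated in terms of standardized differences through Cohen's delta", "expecting large differences (0.95) between groups", and comes to 25 per group after a 5% allowance for dropout. Power and sidedness are not given.

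Section 5.4.1 (Primary outcomes, self-perceived health-related quality of life) describes what the questionnaires produce:

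- EQ-5D-5L gives a weighted summary index. In addition, "The questionnaire also includes a visual analogue scale", scored 0 to 100. Neither is named as the primary measure.
- The catheter questionnaire has 47 questions at the initial visit, which serve as baseline data. The follow-up form repeats them and adds four about information received ("total 51 questions"). For quantitative use, "statements will include single answers with scores on a scale from 0 to 10, 0 to 5, and 0 to 4". No total or domain score is described. The instrument is not yet validated; validation is expected during this trial together with a separate study.

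Section 5.7 (Analysis plan) does not mention 2.5%. It describes comparisons between the groups, refers to 95% confidence intervals, and prints p < 0.005 as the threshold for significance. It defers detail to a statistical analysis plan due before data lock.

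**The concern.** Halving 5% because there are two questionnaires is a Bonferroni split, and such a split must count tests. The protocol counts instruments. One of them, EQ-5D-5L, yields two numeric results by the protocol's own account. The other is described only at the level of single answers on scales of different length. A reader of 5.3 and 5.4.1 therefore cannot tell which two results the two shares of 2.5% are meant for.

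Two things are at stake. First, if more than two results are tested at 2.5%, the split no longer does what it was introduced to do, and a positive primary finding could rest on whichever result crossed the line. The catheter score is the more exposed part: the instrument is unvalidated, patients and clinical staff know the allocation, and the scoring may be settled as late as data lock, when responses already exist. Second, the level that justifies the sample size is not the level printed for the analysis, so the trial's power depends on which section is followed.

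**Working it through.** **Inputs.** From 5.3: level 0.025, standardised difference d = 0.95, 25 per arm, 5% dropout. From 2.3: "Participants will be assigned 1:1 to one of the two trial arms". Assumed, because the article does not state them: two-sided tests and 80% power. The correlations used below are illustrative.

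**Step 1: reproduce the plan's figure.** Normal approximation: n = 2(z₀.₉₈₇₅ + z₀.₈₀)² / d² = 2(2.241 + 0.842)² / 0.9025 ≈ 21.1, so 22 per arm. The two-sample t-test needs 23. Allowing for dropout, 23 / 0.95 = 24.2, so 25 per arm. The stated size is reproduced exactly, which suggests that the 2.5% level drives it. Other combinations land close: for example, a two-sided 0.05 level with 90% power gives 26 (normal) or 27 (t-test).

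**Step 2: family error at 2.5% per test.** For k independent tests it is 1 − 0.975ᵏ.

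- k = 2 (one score per questionnaire): 1 − 0.975² = 4.9%.
- k = 3 (index, VAS, one catheter score): 1 − 0.975³ = 7.3%. The Bonferroni bound is 3 × 2.5% = 7.5%.

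Positive correlation lowers the three-test figure. Simulation with equally correlated normal statistics (200,000 draws) gives:

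| Common correlation | Family error, 3 tests at 2.5% |
|---|---|
| 0.3 | 7.1% |
| 0.5 | 6.6% |
| 0.7 | 5.7% |
| 0.9 | 4.4% |

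The excess over 5% disappears only when the three results are very strongly correlated.

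**Step 3: the threshold printed in 5.7.** At 0.005 per test, three independent tests give 1 − 0.995³ = 1.5%, and ten give 1 − 0.995¹⁰ = 4.9%. Error control is then ample, but power is not. Completers are 25 × 0.95 = 23.75, about 24 per arm. The noncentrality is 0.95 × √(24/2) = 3.29 on 46 degrees of freedom, and two-sided t-test power is:

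- at 0.025: 83%;
- at 0.005: 63%.

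At 0.005, 80% power would need 32 completers per arm, and 32 / 0.95 = 33.7, so 34 enrolled. If 0.05 was meant, as the 95% interval beside it might suggest (an assumption), two tests would give 1 − 0.95² = 9.8% and three 1 − 0.95³ = 14.3%. On neither reading does 5.7 apply the level used in 5.3.

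**Step 4: cost of keeping three primary scores.** Bonferroni over three is 0.05 / 3 = 0.0167. At 80% power the t-test needs 25 completers per arm, and 25 / 0.95 = 26.3, so 27 enrolled, two more per arm than planned. With two scores at 2.5%, no change in size is needed.

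**The case against.** The strongest reply is that 5.3 most naturally means one test per questionnaire, in which case the split works (4.9%). The scoring could legitimately sit in the statistical analysis plan or in the supplementary questionnaires, neither of which is shown. That stands as far as it goes: the absence of a scoring rule from a condensed article is not in itself a fault. But the article itself fixes the multiplicity rule, ties it to the number of instruments, and then describes more than two results under primary outcomes.

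A reader might infer that all 47 or 51 catheter questions are tested separately, which would imply a very high family error. The document does not support this. Nowhere does it say that items are tested one by one. The 47-question form is baseline data. Some questions concern the type of catheter and accessories and need not be numeric, so the number of scored items is unknown. Nor is a raw sum across the three scales planned, or a 51-item total set against a 47-item baseline.

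The threshold sentence in 5.7 follows text about the comparability of the groups, so its reach is arguable. It is nevertheless the only analysis threshold printed.

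The risk of a score chosen to suit the data is also tempered. The analysis is blinded to arm, the analysis plan precedes data lock, a separate validation study is foreseen, and the Discussion openly names the lack of validation as a limitation. These safeguards reduce the risk. They do not fix how many results are tested, and data lock comes after responses have been collected.

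**Conclusion.** The concern holds conditionally. The 2.5% level controls the primary family error at 5% only if each questionnaire contributes one prespecified score, and the article does not name those two scores. Testing one further result, the VAS, is enough to break the control, unless correlation is very high. That excess is modest, at most 2.5 percentage points by the Bonferroni bound, and it would grow if several catheter items were tested. A flat statement that the family error is not held at 5% would go too far, since a single score per questionnaire would hold it.

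The mismatch between 5.3 and 5.7 is independent of that condition and matters more for power: applying the printed 0.005 to a trial sized at 0.025 costs about 20 percentage points (83% to 63%).

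The power figures assume two-sided t-tests and that d = 0.95 is true. This does not invalidate a pilot, but it should be corrected because the quantitative primary claim depends on it.

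**What to change.** In 5.3, 5.4.1 and 5.7, name exactly two primary scores, each tested at 2.5%:

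1. The EQ-5D-5L index at week 4, with the VAS as a secondary outcome.
2. One catheter-questionnaire score built from the numeric items common to both versions, put on a common scale and in the same direction. A mean of items rescaled to 0–100 is one example. Such a mean presumes that the items can sensibly be combined, so the separate validation study may support a different single score. The four added information questions stay out, and single items are reported descriptively.

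Fix the scoring before any follow-up responses are examined, using baseline responses or the separate validation study, rather than relying on data lock as the deadline. Reconcile the threshold in 5.7 with the 2.5% in 5.3, and state the power and sidedness assumed.

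The cost is wording in the protocol and analysis plan, with no extra patients or data. The family error is then 4.9% and power about 83% with 24 completers per arm. The small downside is that VAS and single-item results become secondary or descriptive.

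### The equal 2.5% split used to size the two questionnaires is valid but, if carried into testing, is dominated by Holm; section 5.7 does not carry it forward and states p < 0.005 instead

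*Protocol article*

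**What the plan says.** Section 5.3 (Sample size determination) says that the size "has been calculated in terms of standardized differences through Cohen's delta". It sets the level as "Assuming a significance level of 2.5%, given that the endpoint is composed of two different questionnaires", the effect as "expecting large differences (0.95) between groups", and concludes that "a sample size of 25 per group would be enough, taking into account a dropout rate of 5"%. Section 2.3 (Random assignment) gives equal allocation: "Participants will be assigned 1:1 to one of the two trial arms". Power, sidedness and the correlation between the questionnaires are not stated. One effect size is given for both.

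Section 5.7 (Analysis plan) leaves the detailed analysis to a statistical analysis plan, to be finished before data lock, and rules out imputation. Its only significance threshold is p < 0.005, beside a 95% confidence interval. That threshold closes a paragraph on the comparability of the groups, so it is unclear whether it is meant for the primary comparison. Neither section mentions passing alpha from one questionnaire to the other.

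**The concern.** Two questionnaires share a 5% error rate by halving it. If each is then judged at 2.5% whatever happens on the other, a questionnaire with p between 0.025 and 0.05 is declared non-significant even when the other has clearly succeeded. Holm's procedure tests the smaller p-value at 2.5% and, if that is significant, the other at 5%. It holds the family error at 5% under any correlation and rejects everything that the fixed split rejects, and sometimes more. With 50 patients and no imputation, the difference in power is worth having.

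The level used for sizing and the threshold in the analysis section also differ by a factor of five (0.025 against 0.005). As the article stands, the decision rule for the primary questionnaires cannot be read from it.

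**Working it through.** **Inputs.** From 5.3: alpha 2.5% per questionnaire, standardized difference 0.95, 25 per group, 5% dropout. From 2.3: 1:1 allocation. Assumed because not stated: two-sided t-tests, 80% power, the same 0.95 on both questionnaires, correlation 0 to 0.9.

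**Step 1: reproduce the plan's figure.** The power of a two-sample t-test comes from the noncentral t distribution with noncentrality 0.95 × √(n/2) and 2n − 2 degrees of freedom. At two-sided 0.025, n = 22 gives 79.2% and n = 23 gives 81.3%, so 23 per group are needed for 80%. Allowing for dropout, 23 / 0.95 = 24.2, rounded up to 25. The stated size reproduces.

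**Step 2: evaluable patients.** 25 × 0.95 = 23.75, taken as 24 per arm.

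**Step 3: power per questionnaire at 24 per arm.**
- At 0.025: p25 = 83.1%
- At 0.05: p5 = 89.6%
- At 0.005, if the threshold in 5.7 were applied: 63.4%

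**Step 4: chance of showing both, independent questionnaires.**
- Fixed split: p25² = 0.8312² = 0.691
- Holm: p25² + 2 × p25 × (p5 − p25) = 0.691 + 2 × 0.8312 × (0.8964 − 0.8312) = 0.691 + 0.108 = 0.799

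**Step 5: correlated questionnaires, by simulation (24 per arm, 0.95 on both).**

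| Correlation | Both, fixed split | Both, Holm | At least one, either rule |
|---|---|---|---|
| 0 | 69.0% | 79.9% | 97.1% |
| 0.3 | 71.2% | 81.0% | 95.1% |
| 0.5 | 72.9% | 81.9% | 93.3% |
| 0.7 | 75.2% | 83.2% | 91.1% |
| 0.9 | 78.6% | 84.8% | 87.8% |

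The gain runs from 11 points at correlation 0 to 6 points at 0.9. At correlation 0.5 the power for each single questionnaire rises from 83% to 88%. The last column is the same under both rules because Holm's first step is also at 2.5%.

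**Step 6: sensitivity.** With 23 evaluable per arm, the chance of showing both goes from 66.1% to 77.5% (correlation 0) and from 76.4% to 83.0% (correlation 0.9). With 25 it goes from 72.0% to 82.2% and from 80.6% to 86.4%. If one effect is 0.6 instead of 0.95 (correlation 0.5, 24 per arm), the power for that questionnaire rises from about 41% to 51%.

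**Step 7: error rate.** With no effect on either questionnaire, Holm's simulated family error is 4.96% at correlation 0 and 4.76% at 0.5.

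**The case against.** The strongest objection is that 5.3 fixes no test. "Assuming a significance level of 2.5"% is the level used for sizing, and a trial that intended Holm would size at 2.5% too. A reader might infer that the protocol commits the sponsor to a fixed Bonferroni rule and discards power. The document does not go that far: it nowhere says that each questionnaire is judged only at 2.5%, and it defers the analysis to a plan not shown here, which may already contain a step-down. This stands, and it is why the point is conditional on the split being carried into testing.

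It also stands that an equal split is valid, so nothing in 5.3 is an error. The fixed split has one real advantage: simple simultaneous 97.5% intervals, which Holm does not give. The change is therefore not wholly free.

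Finally, Holm for two hypotheses needs two scores. Section 5.4.1 describes an index and a visual analogue scale for EQ-5D-5L, and 47 or 51 questions on several scales for the catheter questionnaire, without saying which score is primary. This also stands, and the fix has to cover it.

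The objection does not remove the need to act. Section 5.7 prints a threshold that disagrees with 5.3, and the testing rule can be written in the same edit.

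**Conclusion.** The point holds as an efficiency improvement tied to a reconciliation. The 2.5% in 5.3 and the p < 0.005 in 5.7 do not agree, and the latter, if applied to the primary questionnaires, would leave about 63% power for each. Once they are reconciled, Holm is preferable to a fixed split: 6 to 11 points more chance of showing both questionnaires, the same chance of showing at least one, the same family error and the same 25 per group.

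A reader might take 73% to 82% as the trial's own power. It is not. It is the case of correlation 0.5 with 24 evaluable per arm, two-sided t-tests and 0.95 on both instruments. The correlation and sidedness are not in the protocol, and the common effect is an assumption. The range 69–79% to 80–85% should be quoted with those conditions.

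**What to change.** 1. In 5.7, reconcile the p < 0.005 with the 2.5% in 5.3, and say which comparisons the threshold covers.
2. Name one primary score for EQ-5D-5L and one for the catheter-related questionnaire.
3. State in 5.3, 5.7 and the statistical analysis plan, before data lock, that the two scores are tested by Holm at a two-sided 5% family level: the smaller p-value at 2.5% and, if significant, the other at 5%.
4. Report a 95% interval for each difference, labelled as marginal and not simultaneous.

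The cost is a few sentences. The sample size stays at 25 per group because the first step is still at 2.5%. The one thing given up is the simple simultaneous 97.5% intervals that go with the fixed split.
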